### Procedure for part 2: cluster randomised controlled trial

ICUs enrol in the RCT after completing the laboratory experiment on the pain indicators (Fig. 3). Each ICU will receive one educational outreach visit aimed at explaining the dashboard functionalities, how data should be interpreted and how action plans can be developed. The visits will be undertaken by one of two NICE investigators ([name] or WG) with a non-medical but QI background. Further, brief semi-structured telephone calls will be held monthly with each ICU’s contact person to gain progress reports, motivate them to continue using the intervention and provide technical assistance if necessary. The structure of the visits and monthly calls will be the same for all ICUs, with the exception that the action implementation toolbox and its contents will not be mentioned to teams in the control arm. ICUs will participate in the RCT from 6 to 9 months.

#### Randomisation and allocation

We will randomly allocate participating ICUs to receive “A&F only” or “A&F with action implementation toolbox” in a 1:1 ratio. We will randomise ICUs using a block randomisation, with randomly permuted blocks of two or four each consisting of an equal number of interventions and controls. A researcher, who is otherwise unaffiliated with the study and blinded to the identity of the units, will perform the randomisation according to a computer-generated random schedule produced using an R script (R Foundation for Statistical Computing; Vienna, Austria) before the study starts. The size and the contents of the randomisation blocks will be concealed from the investigators enrolling the ICUs. Participants will not be told explicitly what aspect of the intervention is randomised; they will only be aware that there are two variations of providing A&F. Due to the character of the intervention, it is not possible to blind the investigators.

### Sample size

Sample size calculations for the RCT were based on pilot data of pain measurements from six ICUs (five teaching and one non-teaching) in 2014. Based on these data, the mean performance score for pain management is expected to be 76% with a standard deviation of 0.05%. We assumed a cluster size of 300 patient shifts per ICU per 3 months (3 months × 10 average number of patients × 10 average length of stay in shifts). The control arm, receiving only A&F, is expected to increase performance by a median of 4.3% (absolute improvement) based on the Cochrane review of previous A&F studies [18]. To have 80% power to find a difference in performance score for pain management of 10% using a two-sided unpaired *t* test with α = 0.05 would require a total of 24 ICUs to participate in the study.

We did not perform a sample size calculation for the laboratory experiment (study part 1) because this experiment will be conducted in the context of the RCT.

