## Background

Yearly, approximately 90,000 critically ill patients are admitted to Dutch intensive care units (ICU) [1]. During their time in the ICU many patients are exposed to adverse experiences; acute pain being a leading stressor [2]. Physical and psychological stresses caused by pain have been associated with increased length of stay, morbidity and poor mental health outcomes [3–5], and affect quality of life even after ICU discharge [6, 7]. Interview studies revealed that almost half of ICU patients experience moderate to severe pain both at rest as well as during procedures [8–11]. There remains a large gap between ideal and actual care with respect to pain management in intensive care, making it a suitable target for quality improvement (QI) strategies, such as audit and feedback (A&F) [12–15]. A&F has been defined as a “summary of clinical performance in a specific area with or without recommendations for action” [16] and aims to support physicians in accurate self-assessment [17].

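### The sample size of 24 ICUs does not follow from its stated inputs: the printed SD is impossible, and with the likely SD of 5 points the stated 10% difference needs 12 ICUs

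*Protocol article*

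**What the plan says.** All the inputs stand in the Sample size section of the protocol article. Pilot data from six ICUs lead to the statement that "the mean performance score for pain management is expected to be 76% with a standard deviation of 0.05"; the figure carries a per cent sign. On cluster size: "We assumed a cluster size of 300 patient shifts per ICU per 3 months", built up as 3 months × 10 patients × 10 shifts per stay. The control arm is expected to gain 4.3 points in absolute terms, taken from a Cochrane review.

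The target is then given: "To have 80% power to find a difference in performance score for pain management of 10% using a two-sided unpaired" t test at α = 0.05 "would require a total of 24 ICUs to participate in the study". The section on randomisation fixes a 1:1 ratio, so 24 means 12 per arm. The text does not say whether the 10% is the difference between arms or the rise from baseline in the toolbox arm. It states no ICC.

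**The concern.** A reader should be able to put the stated SD, difference, test, α and power into a standard formula and obtain 24. Here that fails twice. The SD as printed cannot describe ICU scores, and the obvious repair (5 points instead of 0.05) gives half the stated number of ICUs.

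What is at stake is how the result will be read. The section on implications for practice and research says that a negative trial would suggest revising the toolbox or turning to other or more intensive approaches. That inference depends on the size of effect the trial could have detected, which is the number left open.

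**Working it through.** **Inputs.** From the Sample size section: mean 76%, SD printed as 0.05%, 300 shifts per ICU, control gain 4.3 points, difference 10%, two-sided unpaired t test, α = 0.05, power 80%, 24 ICUs. From the randomisation section: 1:1, so n = 12 per arm. t-test power is computed from the noncentral t distribution with 2n − 2 degrees of freedom and noncentrality d / (SD × √(2/n)).

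**Step 1: the SD as printed.** Even if every ICU had the same true performance, a score based on 300 shifts would vary by √(0.76 × 0.24 / 300) = 0.0247, or 2.47 points. That is about 50 times the printed 0.05 points. A sampling error of 0.05 points would need 0.76 × 0.24 / 0.0005² ≈ 730,000 shifts per ICU.

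**Step 2: the plan's own figure, with SD 5 points and a difference of 10 points.**
- t test: 5 per arm gives 79.1% and 6 per arm gives 87.6%, so 12 ICUs in total.
- 12 per arm (24 ICUs) gives 99.7%.
- Reading 10% as relative (7.6 points) gives 8 per arm, or 16 ICUs.

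None of these gives 24.

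**Step 3: routes that do give 24.** Each changes something printed beyond the unit of the SD.
- *Route A: difference 10 − 4.3 = 5.7 points, SD 5.* The normal approximation is 2 × (1.96 + 0.8416)² × 25 / 5.7² = 12.08 per arm, with 79.7% power at 12 per arm. The t test that the plan names gives 76.1% at 12 per arm, 79.6% at 13 and 82.7% at 14, so it needs 28 ICUs. With 24 ICUs and SD 5, the difference detectable with 80% power is 5.98 points.
- *Route B: difference 10 points, SD about 8.0 to 8.36.* The t test reaches exactly 80% at 12 per arm when the SD is 8.36. One way to arrive here is to read 0.05 as an ICC and compare 80.3% with 90.3%. The average binomial variance is (0.803 × 0.197 + 0.903 × 0.097) / 2 = 0.1229. The ICU-level SD is √(0.1229 × (1 + 299 × 0.05) / 300) = 0.0808, or 8.08 points. The t test then gives 78.8% at 11 per arm and 82.5% at 12, so 24 ICUs is the smallest design.

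**Step 4: how much the SD matters.** Power of the two-sided t test with 12 ICUs per arm:

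| SD (points) | 10 points | 5.7 points |
|---|---|---|
| 4 | >99.9% | 91.5% |
| 5 | 99.7% | 76.1% |
| 6 | 97.4% | 60.4% |
| 8 | 83.3% | 38.6% |
| 10 | 64.9% | 26.7% |
| 12 | 49.7% | 20.0% |

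If the SD of six ICUs is 5 points, its 95% interval (chi-square, 5 df, normal scores assumed) is 3.1 to 12.3 points. The table lies almost wholly inside that interval.

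**Step 5 (secondary): cluster size.** The Background gives about 90,000 Dutch ICU admissions a year, and the implications section treats 83 ICUs as all those in the country. That is 90,000 / 83 / 12 ≈ 90 admissions per ICU-month, against the assumed 10. At 10 shifts per stay it is about 2,700 shifts per quarter, against 300.

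**The case against.** The strongest defence is that 24 may be correct. Route B uses the stated 10%, the 4.3%, the 300 shifts, the t test and the 80%, and needs only a wrong label on 0.05. On that reading the trial has about 80% power for 10 points, as claimed. Route A, by contrast, leaves the 300 shifts unused and needs a normal approximation in place of the named test. This stands: 5.7 points is an inference, and nothing in the document establishes it as the planned difference.

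A reader might also infer that the trial has 76% power instead of 80%. The document does not support that as a finding. It depends on route A and on an SD of exactly 5.0. The printed figure has one significant digit; for 5.7 points with 24 ICUs, an SD of 4.5 gives 84.3% and 4.76 gives 80.0%. Nor is it the power of the planned analysis, which is a mixed-effects logistic model on patient shifts with a time-by-arm term.

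On cluster size, if the SD is the observed between-ICU SD, the 300 shifts do not enter the t test, and more shifts would only reduce sampling error. A restriction to eligible patients could explain part of the gap, though none is stated. That point is therefore minor.

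None of this rescues the printed statement. Every route to 24 needs the SD replaced or relabelled, and route A also needs a different difference.

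**Conclusion.** The sample-size statement does not reproduce. Two parts are certain given the printed inputs: an SD of 0.05% is impossible for an ICU score on 300 shifts, and SD 5 points with a 10-point difference requires 12 ICUs by the named test, not 24. That 0.05 means 5 points is probable; that it was an ICC is possible.

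The consequence is an ambiguity of about 6 against about 10 points in the effect detectable with 80% power. It would go too far to say that 24 follows only from 5.7 points, or that the 80% claim for 10 points fails on every reading: with an SD of about 8 points it holds. The figures assume equal arms, a common SD and ICU-level scores compared by a t test, as the section states. Conduct, randomisation and analysis are unaffected.

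**What to change.** In the Sample size section:

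1. Give the SD or ICC actually used, with its unit.
2. State whether the 10% is the difference between arms or the rise from baseline in the toolbox arm, and give the two expected arm means.
3. Restate t-test power and the detectable difference for 24 ICUs under those inputs: 76% power and 6.0 points detectable if 5.7 points with SD 5 was used; 99.7% power if 10 points with SD 5; about 80 to 83% if 10 points with an SD of about 8. The sponsor must say which applies; 5.7 points should not be written in as the planned difference unless the original calculation shows it.
4. Show power over a range of SDs, since the estimate comes from six ICUs.
5. Reconcile 10 patients per ICU-month with the roughly 90 implied by the national figures, or state the restriction that explains the gap.

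The cost is restated figures and a short table. No additional ICUs are needed for the correction; if route A was used, the stated power becomes slightly less favourable.

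### The 24 ICUs do not follow from the printed SD, the 10% difference and the t test; at least two readings give 24, and they imply different detectable effects

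*Protocol article*

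**What the plan says.** The Sample size section of the protocol article takes its inputs from pilot data on six ICUs: a mean performance score of 76%, an SD printed as 0.05%, and 300 patient shifts per ICU per 3 months. Of the comparator arm it says that it "is expected to increase performance by a median of 4.3% (absolute improvement"), citing a Cochrane review. The target is worded as follows: "To have 80% power to find a difference in performance score for pain management of 10% using a two-sided unpaired" test (Student's t). At an alpha of 0.05, the total that the section arrives at is 24 ICUs. Randomisation and allocation gives a 1:1 ratio, so 24 ICUs means 12 per arm.

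The section does not say that 4.3 is subtracted from 10. It does not say how the 300 shifts enter the calculation, and it gives no intracluster correlation.

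**The concern.** The difference, SD, test, alpha, power and number of ICUs are all stated, so the claim can be checked without any detail left to an analysis plan. It does not check. Either the variance parameter or the difference is not the one behind the 24, and possibly neither is.

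The stake is how the main comparison will be read. The trial exists to contrast feedback with and without the toolbox, and the Discussion (Potential implications) says that a negative result will point to revising the toolbox. That inference depends on the between-arm effect that 24 ICUs could detect. A reader told 10 points will judge a null result, or a difference of 5 to 6 points, differently from one told 5.7 points.

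**Working it through.** **Inputs** (Sample size; Randomisation and allocation): two-sided alpha 0.05; power 80%; stated difference 10 points; control gain 4.3 points from 76%, giving 80.3%; SD printed as 0.05%; 300 shifts per ICU; 12 ICUs per arm. Power for the unpaired t test with n per arm uses the noncentral t with 2n − 2 degrees of freedom and noncentrality d × √(n/2), where d = difference/SD.

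**Step 1. The plan's own figure from its printed inputs.**
- SD literally 0.05 points: d = 10/0.05 = 200, and 2 ICUs per arm suffice. This is not a credible between-ICU spread.
- SD read as 0.05 on the 0–1 scale, that is 5 points (an assumption): d = 10/5 = 2.0. Power is 0.791 at 5 per arm, 0.876 at 6 and 0.997 at 12. So 12 ICUs in total are enough, and 24 give 99.7%.
- Normal approximation at 10 points: 2 × (1.960 + 0.842)² / 2.0² = 3.92, so 4 per arm (8 in total).
- Adding binomial variance at 300 shifts (SD 5.57) gives 7 per arm. A change-score SD of 7.07 gives 9 per arm.

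None of these gives 12 per arm.

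**Step 2. What SD would make the sentence true?** At 12 per arm, 80% power by t test needs d of about 1.197. For 10 points that is an SD of 10/1.197 = 8.4 points. The document gives no such figure.

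**Step 3. Reading (a): 10% is the toolbox arm's gain over baseline.** The between-arm difference is then 10 − 4.3 = 5.7 points (86.0% against 80.3%), with SD 5 and d = 5.7/5 = 1.14.
- Normal approximation: 2 × (1.960 + 0.842)² / 1.14² = 12.08 per arm, 24.16 in total. This is 24 by ordinary rounding and 26 if each arm is rounded up.
- Named t test: power 0.761 at 12 per arm, 0.796 at 13 and 0.827 at 14. Thus 24 ICUs give 76%, and 80% takes 28. A simulation of 200,000 trials gave 0.759 at 12 per arm.
- Difference detectable with 80% power at 12 per arm: 1.197 × 5 = 6.0 points.

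**Step 4. Reading (b): 0.05 is an intracluster correlation and 10 points is the between-arm difference.** The arms are 80.3% and 90.3%.
- Mean p(1 − p) = (0.803 × 0.197 + 0.903 × 0.097)/2 = 0.1229.
- Variance of an ICU's proportion = 0.1229 × (0.05 + 0.95/300) = 0.00653, so the SD is 8.08 points and d = 10/8.08 = 1.237.
- t test: power 0.788 at 11 per arm and 0.825 at 12. The smallest number is 12 per arm, 24 in total.
- A 5.7-point difference on this reading: mean p(1 − p) = (0.803 × 0.197 + 0.860 × 0.140)/2 = 0.1393, SD 8.61 points, d = 0.66, and power at 12 per arm is about 34%.

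| Reading | Between-arm difference | Variance input | Power of t test, 24 ICUs |
|---|---|---|---|
| Stated difference, SD as 5 points | 10 points | SD 5 | 99.7% |
| (a) | 5.7 points | SD 5 | 76% |
| (b) | 10 points | ICC 0.05, 300 shifts | about 83% |

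**The case against.** A reader might infer that 24 comes only from 5.7 points, so that the trial has 76% power and the 10% should simply be relabelled as the toolbox arm's gain. There is support for this. The 4.3 would otherwise play no part in a t test of a 10-point difference, and the arithmetic lands on 24.16. A two-proportion calculation at 80.3% against 86%, with a design effect derived from SD 0.05, also rounds up to 12 per arm (11.5).

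The document does not establish it. Reading (a) needs the SD rescaled by 100, a subtraction that is not written, a normal approximation in place of the named test, and 24.16 rounded down. It also leaves the 300 shifts unused. Reading (b) keeps the stated 10-point difference and the named test, and uses the 300. It too is an assumption: it relabels as an intracluster correlation what the text calls a standard deviation. It also depends on the control level, since 76% against 86% would need 14 per arm. So 76% is the power on one reading, not a fact about the plan. Writing 5.7 points into the protocol on inference could be badly wrong, because reading (b) gives only about 34% power for that difference.

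Two further objections have weight. On reading (a) the shortfall is modest: 4 power points, or 6.0 points detectable instead of 5.7. Also, the Statistical analysis section plans a shift-level mixed-effects logistic model with a time-by-arm interaction, so no t-test figure is exactly the power of the main analysis. Neither objection makes the printed inputs yield 24.

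**Conclusion.** The point holds in this form: the printed SD, the 10% difference, the two-sided t test at 80% power and the 24 ICUs cannot all be right. That conclusion needs no guess about intent. It holds with the SD taken literally (2 per arm) and with the SD read as 5 points (6 per arm against the 12 planned).

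What the 24 ICUs can detect is not settled by the document. It is 76% power for 5.7 points under reading (a), or about 83% for 10 points under reading (b). The first assumes SD 5 and the unwritten subtraction; the second assumes that 0.05 is an intracluster correlation. Other combinations may exist. Confidence is high that the statement is wrong and low as to which input is at fault. The statement needs correcting because the detectable between-arm effect governs how the primary result is read.

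**What to change.** In the Sample size section, from the original calculation:
1. Correct the variance parameter: an ICU-level SD in percentage points, or an intracluster correlation with the 300 shifts per ICU.
2. State whether 10% is the between-arm difference or the toolbox arm's expected gain over the 76% baseline, and give the two expected arm proportions.
3. Restate the power of 24 ICUs, or the difference detectable with 80% power, for the named t test under those inputs.

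If reading (a) was used, the sentence would say that 12 ICUs per arm give 76% power for 5.7 points (86.0% against 80.3%, SD 5 points), with 80% reached at 6.0 points. If reading (b) was used, it would give the intracluster correlation of 0.05, 80.3% against 90.3%, and about 83% power. If neither was used, give the SD; about 8.4 points is what 24 ICUs, 10 points and 80% power imply.

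The cost is a few restated figures. No extra ICUs and no design change are needed. The price is that the stated power may become less favourable.

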### Statistical analysis

Descriptive statistics will be calculated for all variables of interest. Categorical variables will be summarised using counts and percentages. We will use mixed-effects logistic regression analysis for the main analysis in both parts of the study.

To assess the influence of A&F on self-assessments and improvement intentions (laboratory experiment in part 1), we will use a binary “A&F received” covariate. To adjust for correlations between repeated observations within participants we will add a random intercept for “participating professional”. To adjust for clustering effects within ICUs and around quality indicators, we will add random intercepts for “ICU” and “quality indicator”.

To assess the effect of receiving the action implementation toolbox on pain management performance (RCT in part 2), we will use “patient shift” as unit of analysis. We will include the covariates time, study arm and the interaction term time × study arm, while adding random effects to adjust for clustering within ICUs, patients and shifts. If we suspect problems with the randomisation, we will perform tests of imbalance between groups in baseline variables that may influence the outcome, i.e. age, gender, length of stay and severity of disease at patient-level and hospital type and ICU-level. In case of an imbalance (above 5% level for statistical significance), we will conduct a sensitivity analysis adjusted by these variables to test the robustness of our methods [55].

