A Cochrane review of 140 A&F studies [18] concluded that feedback is effective, but with only a median 4.3% absolute improvement (interquartile range 0.5 to 16%). In fact, a quarter of the studies showed negative or no effect. No effect was also found in a previous A&F trial undertaken by the National Intensive Care Evaluation (NICE) quality registry in Dutch intensive care units [19, 20]. A qualitative evaluation explained that physicians experienced several barriers to achieving QI, such as lack of normative standards and benchmarks, inadequate case-mix adjustment, lack of knowledge on how to improve and insufficient allocated time and staff [21]. In attempt to delineate how to most effectively design and deliver A&F interventions, meta-analyses have indicated that A&F may be more effective when baseline performance is low, the source is a supervisor or colleague, it is provided more than once, it is delivered in both verbal and written formats, and when it includes correct solution information, explicit targets, and an action plan [18, 22, 23]. However, there is little information to guide operationalisation of these factors [24], limiting the progress with which we learn how to design and deliver effective A&F interventions [25]. A recent systematic review of electronic A&F trials alone similarly stressed the scarcity of evidence of effectiveness and the underuse of theory [26]. Researchers have consequently called for theory-informed design and evaluation of A&F interventions, and two-armed trials of different approaches to providing A&F to stimulate this progress [27].

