**Fig. 3 Fig3:**
[figure not shown]
Study flow. *ICU* intensive care unit, *RCT* randomised controlled trial, *A&F* audit and feedback

**Table 2 Tab2:** Predefined reasons to be asked if hypotheses posed by Control Theory are violated

Hypothesis violation	Predefined reason
Negative self-assessment but no improvement intention	This indicator is not an important/relevant aspect of intensive care
	Actions will not improve our performance score on this indicator
	We lack the resources/time/knowledge to take action for this indicator
	Me or my colleagues cannot be motivated to take action for this indicator
	The benchmark (median/top 10%) is unrealistic/unfeasible (round 2 only)
	The measured performance score for our ICU is inaccurate (round 2 only)
Positive self-assessment but improvement intention	This indicator is an essential aspect of quality of intensive care
	It is easy to improve our performance score on this indicator
	Our performance is too low (round 2 only)

In the second round, participants are additionally exposed to all detailed performance information for the indicators including their own performance; the median and top 10% benchmarks; and past performance levels. Participants are asked the same as in round 1, but this time based on the feedback information at hand, their performance target (range 0–100%) and intention to improve practice (range yes/no). During this round, if improvement intentions do not match with the performance assessment presented in the dashboard (e.g. room for improvement [yellow icon] but no intention to improve), participants are again asked to explain their choice using the same list of predefined reasons as in round 1, extended with three reasons relating to feedback rejection (Table 2) or free text.

Finally, if there are discrepancies between improvement intentions in the first and second round (e.g. initially participants did not develop intention to improve on a specific indicator, but after receiving feedback they did), participants are asked what feedback elements caused this (measured performance score were higher/lower than expected; benchmarks were higher/lower than expected; there was a green/yellow/red icon; other [free text]).

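### The primary RCT model and the imbalance check do not list each ICU's pre-feedback pain performance as a covariate, although the data exist; the planned test is valid but less efficient than it could be.

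*Protocol article*

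**What the plan says.** The Statistical analysis section takes the patient shift as the unit of analysis in a mixed-effects logistic model and continues: "We will include the covariates time, study arm and the interaction term time × study arm". Random effects for ICU, patient and shift follow. The section does not say how time is coded, whether shifts from before the intervention enter as outcome data, or which coefficient is the toolbox effect.

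The same section gives a closed list for the imbalance check: age, gender, length of stay, severity and hospital type. The check is run only if randomisation problems are suspected, is triggered by significance, and leads only to a sensitivity analysis. Baseline pain performance is not on the list.

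Pre-feedback performance is available. In round 2 of the laboratory experiment, about a month before the teams' first feedback, participants see detailed results "including their own performance; the median and top 10% benchmarks; and past performance levels". The NICE dashboard section says that scores cover the latest 3 months.

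Allocation is by permuted blocks of two or four. Strengths and limitations explains that stratification by hospital type was judged infeasible with so few units. The Sample size section works "using a two-sided unpaired *t* test with α = 0.05" and arrives at 24 ICUs.

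**The concern.** With about 12 ICUs per arm and no stratification, the arms can easily start at different levels of pain management. An ICU's earlier performance is likely to be among the best predictors of its later performance, and it is already collected. If the primary model does not use it well, two things follow. The standard error of the toolbox effect is larger than it need be. And, given whatever imbalance actually occurs, the estimate is pulled by an amount that the planned check would not detect, because baseline performance is not among the variables checked.

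The Background also reports from meta-analyses that "A&F may be more effective when baseline performance is low". That is a cautious statement, but it gives a further reason to expect change to depend on starting level. A random ICU intercept absorbs differences in level; it does not absorb a dependence of change on level.

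**Working it through.** **Inputs from the protocol.** Two-sided α 0.05; 1:1 allocation of 24 ICUs, so 12 per arm; target stated as "To have 80% power to find a difference in performance score for pain management of 10" percent; expected control-arm gain 4.3 points; "the mean performance score for pain management is expected to be 76% with a standard deviation of 0.05" percent.

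**Assumptions.** The printed SD cannot be meant literally, so 0.05 is read as a proportion, or 5 points. It is unclear whether the 10 points are a difference between arms or a gain from baseline; the second reading gives 10 − 4.3 = 5.7 points between arms. Rho, the ICU-level correlation between baseline and follow-up, is not given, so a range is shown. Variances at the two times are taken as equal.

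**The plan's own figure.** ICUs per arm by the normal formula = 2(1.96 + 0.84)² × SD² / difference².
- Difference 10, SD 5: 3.92 per arm, so 8 ICUs in total (12 by the t test). This does not give 24.
- Difference 5.7, SD 5: 12.08 per arm, close to 12. Rounded up, it is 26 in total (28 by the t test).

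The second pair comes nearest to 24 and is used below. That the stated figure does not reproduce exactly is a separate matter and decides nothing here.

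**Standard errors at ICU level**, each multiplied by √(2/12):
- level contrast (follow-up only): SD
- change contrast (pre/post time × arm, arms free at baseline): SD × √(2(1 − rho))
- baseline-adjusted (ANCOVA): SD × √(1 − rho²), with 21 instead of 22 degrees of freedom and a variance factor of about 1.05 for estimating the slope

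**Power, difference 5.7, SD 5 (non-central t):**

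| rho | Level | Change | ANCOVA |
|---|---|---|---|
| 0 | 76% | 47% | 74% |
| 0.3 | 76% | 62% | 78% |
| 0.5 | 76% | 76% | 85% |
| 0.7 | 76% | 93% | 95% |
| 0.8 | 76% | 99% | 99% |

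Before the slope factor, the ANCOVA variance relative to the change contrast is (1 − rho²) / (2(1 − rho)) = (1 + rho)/2. It is therefore lower by 25% at rho 0.5, 15% at 0.7 and 10% at 0.8.

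**At a true 10-point difference, SD 5.** For rho of 0.3 or more, power is at least 97.7% under all three analyses.

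**Chance imbalance.** The SE of the baseline difference between arms is 5√(2/12) = 2.04 points, so its 95% range is ±4.0 points and the probability of a gap above 2 points in either direction is 0.33. For a realised gap d, the expected error is:
- level contrast: rho × d, hence nearly the whole gap when ICU levels are stable
- change contrast: −(1 − rho) × d, which is regression to the mean
- ANCOVA: about zero

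When the toolbox arm starts more than 2 points higher, the mean gap is 3.1 points. The change contrast is then off by −2.2, −1.5 and −0.9 points at rho 0.3, 0.5 and 0.7.

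**Simulation with stable ICU levels plus independent drift.** The level contrast correlated about 0.9 with the chance baseline difference, and the pre/post interaction about 0. The zero follows from that set-up, in which change is independent of starting level. With equal variances the correlation is −√((1 − rho)/2), or −0.59, −0.50 and −0.38 at rho 0.3, 0.5 and 0.7.

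**Validity.** In simulated trials without a toolbox effect, at rho 0.5, all three analyses rejected in about 5%.

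**The case against.** A reader might infer that the plan discards baseline performance and that the toolbox estimate is biased. The document does not support that. It nowhere excludes pre-intervention shifts, and time, arm and time × arm is a usual specification when such shifts are outcome data. The stated hypothesis of larger and faster improvement under the toolbox fits an interaction. On that reading baseline is already used and stable ICU differences cancel, so between-ICU spread in starting level is not the main noise. Randomisation keeps the estimate unbiased over repeated trials, and the test holds its level. Nor does sizing by an unpaired t test show that the analysis ignores baseline. All of this stands.

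The size of the gain also rests on chosen inputs. If ICU levels were stable and shifts independent, 300 shifts at 76% give a binomial error of about 2.5 points, which against an SD of 5 implies rho of about 0.76 to 0.80; at 0.8 the power gain over the change contrast all but vanishes. Patient clustering or ICU drift would lower rho. The formulas describe a linear ICU-level summary with equal periods before and after, so they do not transfer exactly to a shift-level logistic model over 6 to 9 months.

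The objection does not remove the rest. Coding of time may be left to a fuller document, but the article does name its covariates and its imbalance variables, and baseline performance is in neither list. Regression to the mean remains under the interaction reading, and under the arm-coefficient reading most of a chance gap can pass into the estimate.

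**Conclusion.** The point holds as a recommended improvement, not as an error that invalidates the analysis. The listed model and imbalance check omit an available baseline measure in a small, unstratified cluster trial.

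The consequence depends on something the article leaves open. With the arm coefficient on post-randomisation shifts, a chance baseline gap carries over by a fraction rho, almost fully if ICU performance is stable. With time × arm and pre-intervention shifts, what is left is regression to the mean and a variance that adjustment would lower by 25%, 15% or 10% at rho 0.5, 0.7 or 0.8.

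In the illustrative case, adjustment gives 9 points more power than either alternative at rho 0.5. The gain is only about 2 points over the level contrast at rho 0.3 and over the change contrast at rho 0.7. This rests on an assumed rho, an SD read as 5 points and a 5.7-point difference derived here; at a true 10-point difference with SD 5 the choice hardly affects power. Confidence is medium.

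**What to change.** Prespecify one of two forms in the primary model:

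- (a) Enter each ICU's proportion of adequately managed patient shifts over the 3 months before its first exposure to feedback as a fixed ICU-level covariate, for example as a centred logit. Add baseline × time if time × arm is the tested term. The window should close before round 2 of the laboratory experiment, since team members see their results there.
- (b) Model pre-intervention shifts as outcomes and constrain the arms to a common mean at baseline.

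In either case, state how time is coded, which shifts enter and which coefficient is the toolbox effect. Report the model without baseline adjustment as a sensitivity analysis.

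This takes a few sentences in the analysis section or SAP and needs no new data or ICUs. It uses one or two of about 22 ICU-level degrees of freedom. If baseline were uncorrelated with follow-up, the loss against the level contrast would be about 2 points of power (76% to 74% in the case above).
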